## Discussion

### Summary

Our study addresses the overlapping challenges of alcohol use and HIV among PLW in a high-burden setting by developing and piloting MM+, an adapted, community-informed version of the MM model. Through a phased, participatory approach grounded in the ADAPT-ITT framework and community-based research principles, MM+ integrates alcohol reduction with HIV prevention and treatment using a HIV seroneutral approach. The intervention is designed to reflect the real-world needs of PLW, their partners, health care providers, and communities.

Although PLW face increased risks related to both HIV and alcohol use, few community-informed interventions have directly addressed these intersecting vulnerabilities. Existing brief interventions to reduce alcohol use during pregnancy have shown limited and short-lived impact, partly due to minimal follow-up and lack of biomarker validation. Evidence from South Africa demonstrates that integrating peer mentor mothers into care structures can improve maternal health outcomes and reduce vertical HIV transmission through task shifting, whereby trained peer mothers deliver counseling and support within routine and community-based care. These MM models, pioneered by mothers to mothers, have primarily focused on preventing mother-to-child HIV transmission and improving maternal-child health, with only limited adaptation to address alcohol or substance use. Although alcohol has not been a central component of MM interventions, prior adaptations illustrate the flexibility and effectiveness of this platform for addressing broader maternal-child health priorities.

Building on this foundation, our study applies the ADAPT-ITT framework to systematically tailor the MM model to explicitly incorporate alcohol use reduction alongside HIV prevention and treatment. By leveraging an established, trusted, and evidence-based delivery platform, we aim to ensure that the adapted intervention is both responsive to community needs and feasible for integration into existing health systems. Through a structured participatory process using rapid qualitative methods, we demonstrated the feasibility of adapting the MM model for the South African context. Findings from formative interviews and a consensus-building workshop highlighted strong stakeholder support for tailoring content, delivery modalities, and session structures to local realities. Participants emphasized the value of integrating women with lived experience as peer mentors, delivering sessions in accessible community-based venues, and addressing both health-related and psychosocial challenges faced by PLW.

### Strengths

This study has several notable strengths. First, it builds on an established, evidence-based MM platform that has been successfully implemented to reduce vertical HIV transmission, increasing the feasibility and sustainability of our adaptation. Second, the intervention is community informed and peer delivered, which enhances cultural relevance, trust, and the likelihood of uptake among PPW. Third, the use of the ADAPT-ITT framework ensures a systematic and theory-driven approach to intervention modification, increasing the rigor of the adaptation process. In addition, incorporating biological markers of alcohol use alongside self-reported measures strengthens the validity of outcome assessment and addresses limitations of prior studies. Finally, the focus on integrating HIV prevention and alcohol reduction within maternal and child health platforms reflects a holistic approach that aligns with existing health system priorities.

### Limitations

Several limitations should be acknowledged. As an adaptation and implementation study, findings will be context specific, and generalizability beyond the study setting may be limited without additional testing. The reliance on peer-delivered counseling may pose scalability challenges in regions with limited MM program coverage or constrained human resources in the current South African context. Although biomarkers improve accuracy, they may not fully capture patterns of alcohol consumption, and social desirability bias in self-reports could remain. Finally, the intervention’s impact on longer-term outcomes, such as sustained alcohol reduction and HIV incidence, will require extended follow-up beyond the study period.

### Conclusion

This pilot trial will assess the feasibility, acceptability, and preliminary impact of MM+, while also generating insights into personal and structural barriers to care. We hypothesize that the intervention will be acceptable among pregnant women and providers and will reduce alcohol use during pregnancy, while also improving access to HIV prevention and care. Findings will inform future scale-up efforts, with the goal of improving maternal and child health through a practical, scalable strategy in high-burden and low- and middle-income settings.

## Data Availability

Data will be available for review upon request to study investigators. The trial protocol and statistical analysis plan can be accessed via the study principal investigators. All data will be disseminated during the study period to the community, participants, and stakeholders through regular meetings. Primary and secondary outcomes, including formative research results, will be communicated through conferences and peer-reviewed manuscripts during and following the trial period.

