### Study Design for the Pilot RCT (January 2026-February 2027)

We will identify and train 3-5 mentor mothers from the community. Inclusion criteria for mentor mothers include women (≥25 years old) in the community with lived experience who are either on PrEP or have HIV and are on ART and who reported reducing or stopping using alcohol during pregnancy. Mentor mothers will be trained on the adapted MM+ curriculum and MI techniques (step 7 of ADAPT-ITT). We will include 10-15 providers (midwives, nurses, and counselors) to be part of the MM+ training and support the integration of MM+ in three antenatal care (ANC) clinics. Concomitant ante- and postnatal care, including HIV testing and ART and PrEP provision, will be provided to all women regardless of study allocation.

Following training, trained study staff in three local clinics and surrounding communities will recruit and enroll 100 pregnant women who report recent (past 2 months) alcohol use to evaluate the effectiveness and feasibility of the MM+ intervention in reducing alcohol use in PLW, PrEP use in PLW without HIV, and ART adherence in PLW with HIV (step 8 of ADAPT-ITT). Participants will be randomized in a 1:1 ratio to the MM+ study arm or enhanced standard of care (SOC). SOC is focused on HIV counseling by peers, without alcohol messaging. If we are unable to identify 100 women in the three select clinics and communities, we will expand to additional communities and clinics.

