#### RCT Outcomes

The RCT primary outcome is the preliminary effectiveness (comparing the MM+ arm to the enhanced HIV attention control arm using intention-to-treat analysis) defined as a reduction in alcohol use via biomarker-confirmed self-reported and biological samples (comparing baseline to 6 months in phosphatidylethanol [PEth] blood samples).

Secondary outcomes include (1) PrEP initiation and adherence (via patient records and urine TFV testing at 6 months) and (2) ART adherence (via urine TFV testing and self-report). In addition, we will evaluate three of the eight implementation outcomes, as defined by Proctor et al [46]: feasibility, acceptability (including participant satisfaction with the intervention), and fidelity. We will also track any social or health harms in the study and relatedness to the study intervention through study surveys and review of medical records. Table 2 describes how these outcomes will be measured. We will track session attendance, as well as ART and PrEP adherence, at each study visit.

**Table 2 table2:** Description of aim 3 implementation outcomes.

Evaluation parameter	Description	Methods	Frequency
Theoretical model	Evaluate changes in alcohol use and HIV prevention or treatment (eg, PrEP^a^ and ART^b^ use) using the theory-of-change model measuring change and which sociodemographic and behavioral characteristics are associated with change in order to understand any subpopulations receptive toward the strategic priorities and pathways of change identified by our model.	Quantitative surveys at each visit and biomarker data	Baseline and 6-month follow-up
Participants’ self-reported fidelity	Evaluate completeness of the intervention through a checklist assessing whether specific topics were covered during intervention sessions, including an assessment of the quality of intervention interactions, where participants will rate implementer engagement during intervention sessions.	Quantitative surveys at each visit and biomarker data	Baseline and 6-month follow-up

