#### Outcome Data Ascertainment

Participants will be followed for 6 months. During this time, they will have three study visits, in which they will self-report alcohol use and PrEP or ART initiation or continuation to study staff. At each study visit, we will ascertain dried blood spots for assessment of recent alcohol use, via PEth testing (PEth<20 ng/mL represents light or no consumption [47]) and AUDIT-C, a validated survey of alcohol use (0=abstinence, >0=recent alcohol use). Participant medical files will be reviewed at the end of the study to ascertain birth outcomes (including any pregnancy loss or stillbirth), reported harms, and PrEP and ART prescription. At each study visit, participants will provide a urine sample to the study staff for analysis of recent PrEP or ART use using urine TFV testing (of recent adherence in the past 72 hours). Urine TFV results will show recent adherence and will be evaluated in conjunction with viral loads (VLs). For those on ART, we will review their files for VLs to evaluate VL suppression at baseline and end of the trial (VL<200 copies/mL). If VLs are unavailable, we will track them online with the national health laboratory service.

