### RCT Inclusion Criteria

Women who are ≥16 years old, with a confirmed pregnancy; who report alcohol use during pregnancy (in the past 2 months); who live within 20 km of the study facility; and who are able and willing to consent to study participation are eligible to participate.

One trained research assistant based at the ANC clinic will screen and obtain informed consent from PLW during their routine ANC visits using a set script for screening participants. We have received a waiver of parental consent for adolescents aged 16 and 17 years.

We will randomize the enrolled participants who have provided informed consent to the MM+ intervention or to enhanced HIV attention control in a 1:1 ratio. Randomization will be performed immediately following enrollment using dynamic permuted blocks with REDCap randomization sequentially. Trained researchers will not have access to the random allocation sequence. The intervention is nonblinded.

All study procedures will be in a private space in the Saldanha Bay municipality clinics, including screening, review, and signing of consent forms, surveys, and other procedures. This space will be dedicated research space given to the Human Science Research Council (HSRC) and FARR teams. We will ask pregnant women who may be interested in the study to see the study staff (in the study room) at the end of their visits or to get an appointment for another day to return to the clinic for study enrollment (if eligible).

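### The dissemination text, read as written, permits emerging outcome results by arm to reach participants and their community while the nonblinded trial is still running

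*Protocol article*

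**What the plan says.** The only text in the article on when outcomes are reported is under Data Availability. It makes two commitments:

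- To the local audience: "All data will be disseminated during the study period to the community, participants, and stakeholders through regular meetings".
- To the scientific audience: "Primary and secondary outcomes, including formative research results" "will be communicated through conferences and peer-reviewed manuscripts during and following the trial period".

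The same section opens with "Data will be available for review upon request to study investigators", with no condition on timing.

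Under RCT Outcomes, the primary outcome is a comparison of arms on reduction in alcohol use, combining self-report with a biomarker ("comparing baseline to 6 months in phosphatidylethanol [PEth] blood samples"). Under Outcome Data Ascertainment, "Participants will be followed for 6 months". Under RCT Inclusion Criteria, "The intervention is nonblinded". The heading of the pilot RCT section dates the trial from January 2026 to February 2027.

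**The concern.** The usual rule is that comparative results stay with an independent monitoring body until outcome collection is complete. The Data Availability text points the other way. It covers all data, names participants and community among the recipients, and places the release during the study. For conferences and papers it lists the period during the trial separately from the period after it.

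What is at stake is operational bias. Women, mentor mothers or clinic staff who hear that one arm looks better or worse may behave differently for the rest of the trial, in whether they enrol, attend sessions, drink, stay in follow-up, or report drinking candidly. PEth resists misreporting, but it does not protect against a real change in drinking prompted by the news. AUDIT-C is open to both.

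**Working it through.** The article gives no figure on this point to reproduce. The check is a reading of the sections together, plus simple calendar arithmetic.

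**1. Is the release limited to formative work?** No. The only primary outcome the article defines is the RCT arm comparison on alcohol use, and the secondary outcomes are PrEP and ART measures in the same trial (RCT Outcomes). Data Availability names primary and secondary outcomes and lists formative results as one part of what is communicated.

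**2. Does another section hold comparative data back?** No. Ethical Considerations sets up a DSMB that meets quarterly on safety and data monitoring, but does not make it the only body to see data by arm.

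**3. Who would hear the results?** Participants, the community and stakeholders (Data Availability). Women are recruited at three local clinics and in the surrounding communities (pilot RCT design section). The Community Advisory Board includes pregnant individuals and providers and advises on implementation throughout (Ethical Considerations).

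**4. Does this cut across the trial's own safeguards?** Yes. Control counselling covers HIV without alcohol content (pilot RCT design section), and control mentor mothers are kept separate from the intervention's to prevent contamination (Enhanced Standard of Care). Presenting emerging alcohol results to a mixed audience of both arms would weaken that separation. The Limitations section already accepts that social desirability bias may remain in self-reports.

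**5. How long could incomplete 6-month results exist?** Inputs: a window of 14 months (January 2026 to February 2027, inclusive) and 6 months of follow-up per woman. Assumptions, not given in the article: enrolment lasts *A* months and starts *d* months into the window, after mentor mothers are trained.

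- First possible 6-month result: month *d* + 6.
- Last 6-month result: month *d* + *A* + 6.
- Span with some but not all results: (*d* + *A* + 6) − (*d* + 6) = *A* months.
- Upper limit if all follow-up fits the window: *A* ≤ 14 − 6 − *d* = 8 − *d*, so at most 8 months.

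With *d* = 0, the last 6-month visit falls at month 10 for *A* = 4, month 12 for *A* = 6 and month 14 for *A* = 8. A later start moves these dates back by *d*. This shows that a period of exposure exists. It does not measure the bias.

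**The case against.** **The text does not say that arm results will be released early.** This is correct. A reader might infer that the plan prescribes reporting the arm comparison before all women reach 6 months. The article mentions no release by arm and no release date. The term study period is undefined. It includes formative work begun in January 2025 (Results) and interviews that come after quantitative analysis (Mixed Methods Analyses, Table 2), so outcomes could be shared within it after the last 6-month visit. The wording about during and after the trial could also mean formative results first and trial results later. The authors may intend only that. What remains is that the text permits the harmful reading and nothing in the article excludes it.

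**Type I error.** A reader might also infer that the false-positive rate is inflated. The article does not support this. It describes one comparison, baseline to 6 months, at two-sided .05, with no interim efficacy test or stopping rule. Release of results followed by a single final test does not by itself add a test. By simulation, testing at .05 on each of two equally spaced looks, with a claim allowed at either, would give about 8.3%, and four looks about 12.6%. Those designs are not in this plan.

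**Embargo and database lock usually sit in the full protocol, analysis plan or DSMB charter.** This is fair, and their absence from an article is no finding. The point here is different: the article makes a positive statement on timing and scope, and that statement is too broad.

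**This is a pilot of preliminary impact.** That limits the consequences. Even so, the arm comparison on alcohol use is the stated primary outcome and is meant to inform scale-up.

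**Conclusion.** The point stands as a wording fault with a real operational risk. The Data Availability section commits to in-study release in terms broad enough to include primary and secondary outcomes by arm, to recipients who include the women under study. In a nonblinded trial with a partly self-reported outcome and deliberate contamination safeguards, that exposes recruitment, attendance, drinking, retention and AUDIT-C answers to influence from emerging results.

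The size of any bias cannot be estimated from the article. The exposure lasts as long as enrolment does, at most 8 months if follow-up is completed inside the stated window. The conclusion rests on taking the sentences as written. If only formative or pooled findings are meant, the text should say so.

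**What to change.** Reword Data Availability along these lines:

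> Formative findings (aims 1 and 2) and pooled, non-comparative recruitment and retention information may be shared while the study is running. Outcome results by study arm will be released to no one except the DSMB until the last randomised woman has completed her 6-month visit and the database is locked. Individual results returned to a participant as part of study procedures, such as point-of-care urine tenofovir feedback, are exempt.

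The exemption is needed because both arms receive urine tenofovir feedback as part of their counselling (Description of the MM+ Intervention; Enhanced Standard of Care). The sentence on data review by request should carry the same time condition.

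The cost is small. Community meetings and conference reports of RCT outcomes wait until follow-up is complete, while formative results can still be shared at once. The Results section lists only preparation for the RCT, so as of the article the change could be made before any outcome data exist.

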## Appendix

Multimedia Appendix 1 Focus group topic guide.

Multimedia Appendix 2 Interview guide.

Multimedia Appendix 3 Peer-review report by PPAH-Population and Public Health Approaches to HIV/AIDS Study Section (National Institutes of Health, USA).

## Abbreviations

ANC: antenatal care
ART: antiretroviral therapy
CAB: Community Advisory Board
FARR: Foundation for Alcohol-Related Research
FASD: fetal alcohol spectrum disorder
FGD: focus group discussion
HSRC: Human Science Research Council
ICF: informed consent form
IDI: in-depth interview
IPV: intimate partner violence
MI: notivational interviewing
MM: Mentor Mother
MM+: Mentor Mother Plus
PEth: phosphatidylethanol
PLW: pregnant and lactating women
PrEP: pre-exposure prophylaxis
RCT: randomized controlled trial
SOC: standard of care
SOP: standard operating procedure
TFV: tenofovir
VL: viral load
